### Exclusion criteria

Individuals are not eligible if they have a medical history of cardiovascular disease, diabetes, endocrine abnormalities, renal disease, contagious skin condition, epilepsy, tumors, mental disorders, are pregnant, have photosensitivity reactions to laser treatment, use a pacemaker, have used medications known to affect one’s weight up to 1 month in advance, or are unwilling to comply with the study protocol.

### Randomization and allocation concealment

After initial assessments, subjects will be assigned to 1 of 2 groups with a 1:1 allocation ratio according to a computer-generated randomization list. The group each subject is allocated to will be concealed in sequentially numbered sealed opaque envelopes. The envelopes will only be opened after the subject has completed baseline clinical assessments. Randomization allocation will be concealed from the physician, subjects and evaluators.

### Interventions

#### Laser acupuncture group

Subjects will receive 24 activated laser acupuncture treatments. Treatments will be performed 3 times a week for 8 weeks. Based on the theory of Traditional Chinese Medicine (TCM) and clinical literature on acupuncture therapy for the obese, the acupoints are as follows: ST25 (*Tianshu*), ST36 (*Zusanli*), ST40 (*Fenglong*), ST44 (*Neiting*), LI4 (*Hegu*), LI11 (*Quchi*), SP6 (*Sanyinjiao*) and PC6 (*Neiguan*). An additional file shows this in more detail (see Additional file 1).

The treatment will be applied by a GaAlAs semiconductor diode Laser Phototherapy Device (Model: T-816-3E2-808) developed by Transverse Industries Co., Ltd, Taipei, Taiwan with a wavelength of 808 nm. Maximum power output is 150 mW in continuous wave mode at a power density of 0.417 W/cm^2^. The laser will be applied for 10 seconds to each of the selected acupuncture points with an energy density of 4 J/cm^2^ for each point. This is the recommended treatment dose for low-level laser therapy as documented by the World Association of Laser Therapy [16, 17].

The laser handheld device (Laser Beam Spot Size ≤ 36 mm^2^) will be applied directly and perpendicularly. There will be slight contact with the skin surface to avoid scattering the laser beam. Apart from the light touch of the laser probe when applied to the skin, no sensations were reported when the device was used in the past.

#### Control group

Subjects in the control group will undergo sham laser acupuncture treatment with no laser power output. Acupuncture points, application duration and total number of treatments will be identical to the experimental group. All laser application will be performed by the same physician.

#### Outcome assessment

Before the treatment, clinical assessment parameters will be evaluated by an evaluator. Post-treatment assessments will be evaluated by a different evaluator. The physician who applies the treatment to the subject will not be involved in assessing the parameters. This way, the subject and both evaluators will be blinded to the treatment being performed.

The primary outcome measurement is the BMI change from baseline. BMI will be calculated using weight (kg)/height (m^2^). Secondary outcome measurements include waist circumference, hip circumference, WHR, body fat percentage, hunger and a Short-Form 36-item Health Survey (SF-36). Waist circumference will be measured at the midpoint between the lower margin of the least palpable rib and the top of the iliac crest, using a stretch‐resistant tape. Hip circumference will be measured around the widest portion of the buttocks, with the tape parallel to the floor [18]. Bioelectrical impedance will be used to measure the percentage of body fat.

For hunger, a Visual Analog Scale (VAS) with horizontal lines will be used, graded from 0 mm, representing no hunger, to 100 mm, representing the most extreme hunger imaginable. Subjects will be asked to mark their level of hunger on the VAS. Subjects will be prohibited from accessing their previous VAS records on subsequent sessions. Measurements of appetite as expressed by ratings on the VAS has been shown to be highly reproducible and reliable for appetite research [19]. These clinical assessments will be performed before the trials, once every 2 weeks during the treatment, and 2 months after the last treatment.

SF-36 is a widely used questionnaire for measuring self-reported physical and mental health status. Each subject will answer the SF-36 questionnaire before the trials, immediately after the trials and 2 months after the last treatment. The SF-36 questionnaire consists of 11 questions concerning general health, and can be divided into two aggregate summary measures: the Physical Component Summary and the Mental Component Summary. The SF-36 has become one of the most widely used measures to evaluate health-related quality of life [20].

Other outcome parameters are skinfold thickness, thigh circumference, blood pressure and heart rate. Skinfold thickness will be measured to the nearest millimeter at six sites (triceps, subscapular, suprailiac, abdomen, thigh and calf) using a caliper [21]. All measurements will be taken from the right side of the body. These skinfold thickness measurements will be taken three times, with the average of the 3 values recorded as the representative value. Previous research has indicated that skinfold caliper and computed tomography are similar with respect to the measurement of subcutaneous body fat [22]. The skinfold thickness measurement at different body sites is important because regional adiposity, rather than total excess adiposity, has a greater impact on certain diseases [23].

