### Statistical analysis

Statistical analysis will be performed by using the software program Statistical Package for the Social Sciences (SPSS 15.0, Chicago, IL, USA). Participants’ demographic information and levels of major measured variables were analyzed by descriptive statistics. Means and standard deviations of the clinical indices will be calculated, after which the evaluation between the two groups will be compared using a Student’s *t*-test. The difference of evaluation scores before and after each examination point will be analyzed using paired *t*-tests. The repeated measures analysis of variance (ANOVA) will be used to analyze longitudinal and repeated measured data for the clinical indices across the 8 data collection points (treatments for 16 weeks, followed-up evaluation biweekly). A value of *P* < 0.05 will be regarded as statistically significant for the above statistical analyses.

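### Because one evaluator measures before treatment and another after, evaluator differences in tape and caliper outcomes are confounded with within-group change from baseline

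*Protocol article*

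**What the plan says.** Outcome assessment sets out who measures: "Before the treatment, clinical assessment parameters will be evaluated by an evaluator", and then "Post-treatment assessments will be evaluated by a different evaluator". The treating physician takes no part in assessment. The arrangement is presented as a blinding measure: "This way, the subject and both evaluators will be blinded to the treatment being performed".

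Several outcomes depend on the operator's technique:

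- Waist: "Waist circumference will be measured at the midpoint between the lower margin of the least palpable rib and the top of the iliac crest".
- Hip: "Hip circumference will be measured around the widest portion of the buttocks".
- Skinfold, by caliper: "Skinfold thickness will be measured to the nearest millimeter at six sites". Replication is planned: "These skinfold thickness measurements will be taken three times, with the average of the 3 values recorded as the representative value".
- Thigh circumference is listed among the other outcomes, and waist-to-hip ratio is derived from waist and hip.

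The Statistical analysis section plans Student's t-tests between groups, a repeated measures ANOVA over 8 data collection points, and a within-group comparison: "The difference of evaluation scores before and after each examination point will be analyzed using paired" t-tests.

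Assessments take place before the trial, every 2 weeks on treatment, and 2 months after the last treatment. The article does not say which evaluator takes the 2-weekly measurements.

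**The concern.** On the plain reading, evaluator and time coincide: one person supplies the baseline value and another the post-treatment value. If one of them places the tape slightly lower, pulls it tighter or pinches a different fold, the difference appears as change in every subject. Since no subject is measured by the same person before and after, these data cannot separate evaluator from change.

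What is at stake is the within-group results. A paired test on waist, hip or skinfold could be significant in either arm with no real change, and could then be read as fat loss or contouring. The Discussion section names regional adiposity and body contour among the questions the trial is meant to answer.

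**Working it through.** The plan gives no figure on this point to reproduce, so the check is a simple measurement model plus an illustration of size.

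**Inputs from the protocol article.** 52 subjects per group and 10% drop-out (Sample size); a two-sided test at 0.05 (Statistical analysis; two-sidedness is my assumption); the evaluator split (Outcome assessment).

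**Inputs assumed, not in the documents.** True change of zero; SD of waist change of 2, 3 or 5 cm; a systematic difference between the two evaluators of 0.5, 1 or 2 cm.

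**Step 1: the model.** Let A be the offset of the pre-treatment evaluator and B that of the post-treatment evaluator. Then

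observed change = true change + (B − A) + random error.

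The mean within-group change is biased by exactly B − A. Averaging three skinfold readings shrinks the random error but leaves B − A untouched.

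**Step 2: rejection rate of the paired test.** With b = B − A and n = 52, the statistic is noncentral t with 51 df and noncentrality b / (SD/√52). The two-sided critical value is 2.008. For SD = 3 cm the standard error is 3/√52 = 0.416 cm, so b = 1 cm gives noncentrality 1/0.416 = 2.40 and a rejection rate of 0.655. All cases:

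| SD of change | b = 0.5 cm | b = 1 cm | b = 2 cm |
|---|---|---|---|
| 2 cm | 42% | 94% | over 99% |
| 3 cm | 22% | 66% | over 99% |
| 5 cm | 11% | 29% | 81% |

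The nominal rate is 5%. With 46 subjects, to allow for drop-out, the SD = 3 cm row becomes 20%, 60% and 99%.

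**Step 3: the between-arm contrast.** If the same two evaluators serve both arms,

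(active change + b) − (sham change + b) = active change − sham change.

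A constant b cancels and adds no variance. A simulation with 46 per arm, SD 3 cm, no true change and 5,000 runs agrees:

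| Offset b | Within-arm paired test, rejection | Between-arm test, rejection |
|---|---|---|
| 0 cm | 5.1% | 4.9% |
| 0.5 cm | 19.8% | 4.7% |
| 1 cm | 60.5% | 4.9% |
| 2 cm | 99.6% | 4.7% |

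The b = 0 row is also what one evaluator per subject would give.

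**Step 4: the repeated measures ANOVA.** The time effect takes up b wherever a visit measured by one evaluator is compared with a visit measured by the other. The group-by-time comparison does not, by the cancellation in Step 3. If the second evaluator takes every visit after baseline, only comparisons with baseline are affected. If the split recurs in each period, the comparison of the end of period 1 with the start of period 2, which would show return towards baseline over the 2-week washout, is confounded with evaluator as well.

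**Step 5: is the split needed for blinding?** Study design states that outcome assessors are blinded to allocation throughout. Randomization and allocation concealment states that allocation is concealed from evaluators. Outcome assessment keeps the treating physician out of measurement. Blinding to allocation is therefore provided for without a change of evaluator.

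**The case against.** The strongest objection is that the trial exists to compare active with sham laser, and this arrangement leaves that comparison intact. That stands. A reader might infer from confounding with change from baseline that the estimated treatment effect is biased, or that evaluator differences add noise to it. The documents support neither: Step 3 shows that a shared constant offset cancels and adds no variance. Extra noise would require evaluator differences that vary from subject to subject, and nothing in the documents quantifies that. The crossover helps further: if the same person takes the post-treatment values in both periods, each subject's post-active and post-sham values share an evaluator.

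Second, the primary outcome is BMI, from weight and height. Body fat is measured by impedance, hunger is self-marked and SF-36 is self-reported. These are far less exposed, and this stands too.

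Third, a reader might conclude that the split serves no purpose. That goes too far. An evaluator who did not take the baseline cannot anchor on a remembered value. The split trades less recall for an inter-evaluator difference; what it does not do is add to blinding to allocation.

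Fourth, the article fixes landmarks, tape type, body side and triplicate skinfolds, which should reduce evaluator differences, and evaluator training is a detail that a full protocol may hold. This makes a large offset less likely but does not make any remaining offset separable from change.

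Fifth, the SDs and offsets are assumed. That is so, and the rates vary widely across them; at 1 cm they exceed 5% at every SD shown.

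**Conclusion.** The point holds for within-group change in operator-dependent secondary and other outcomes: waist, hip, waist-to-hip ratio, thigh circumference and skinfold. There the bias equals the evaluator difference, and it affects planned analyses, namely the paired t-tests and the ANOVA time effect. Under the assumed values, a 1 cm waist offset with no true change gives a significant paired test in about 29% to 94% of trials at n = 52. These rates show sensitivity; they do not predict what this trial will see.

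The conclusion rests on the plain reading that baseline and post-treatment values of a subject come from different people. How far it reaches into the 2-weekly visits cannot be settled, because the article does not say who takes them. It does not extend to the active-versus-sham contrast, provided both arms share the evaluators, nor materially to BMI. It is an avoidable weakness in secondary analyses and does not undermine the trial's main comparison, but it is worth correcting because the remedy is cheap.

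**What to change.** For subjects not yet measured, have the same blinded evaluator take all of a subject's measurements at every visit, including the 2-weekly and follow-up visits, on forms that do not show earlier values. Divide subjects between the two evaluators in balance across the two treatment sequences, and state this in Outcome assessment.

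The trial is already recruiting, so some subjects may have been measured under the split. For them, do not interpret within-group before/after tests of tape and caliper outcomes as treatment effects; base conclusions on the active-versus-sham contrast.

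The cost is some rostering effort, since one evaluator must be available for a subject through two 8-week periods, the 2-week washout (18 weeks in all) and the follow-up visit 2 months later. There is also some risk that an evaluator remembers earlier values, which the forms limit but do not remove. No extra staff are needed.

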### Study design

This study proposes a patient-assessor-blinded, randomized, sham-controlled crossover trial with a 2-week washout period between each crossover phase. The trials will be conducted at the Chiayi Chang Gung Memorial Hospital. This study will adhere to the recommendations of the Consolidated Standards of Reporting Trials (CONSORT) [13] to allow for greater completeness, transparency and accuracy of reporting. The protocol for this study has been registered in the Clinical Trials register (ClinicalTrials.gov Identifier: NCT02167308).

Subjects who voluntarily sign a consent form will undergo the trial according to the study design. When a subject is determined to be fit for participation based on inclusion and exclusion criteria, the subject will be randomly assigned to 1 of 2 groups in a ratio of 1:1. One group is the true laser experimental group and the other is the sham laser control group. Each group will receive their treatment 3 times a week for 8 weeks. After 8 weeks of treatment and a 2-week washout period, the control group will switch to the experimental group while the experimental group will switch to the control group. The subjects then undergo the treatment of their new group for another 8 weeks (Fig. 1).

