#### Follow-up

Follow-up observations will be conducted before the trials, once every 2 weeks during the treatment, and 2 months after the last treatment.

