## Discussion

Obesity is closely linked to many serious health problems and has a profound economic impact on health care systems and society. Current drug treatments for obesity are largely inadequate and there is an enormous unmet clinical need for more safe and efficacious obesity treatments. Laser acupuncture has been shown to have beneficial effects on obesity. However, to our knowledge those trials were either non-randomized, non-blinded, had a limited number of subjects, or included low-calorie diet control. We have, therefore, designed a patient-assessor-blinded, randomized, sham-controlled crossover trial to investigate the effects of laser acupuncture on obesity. A 1-week washout period between treatment sessions was used in a previous randomized crossover study of acupuncture on obesity [24]. We extended this washout period to 2 weeks to further reduce potential carryover effects.

Analysis of skinfold thickness at different body sites, feeling of hunger and quality of life will also be performed. To our knowledge, these secondary outcomes have not yet been measured in similar studies investigating the effects of laser acupuncture on obesity. Through this study we will be able to determine whether or not laser acupuncture can alter regional adiposity, body contour and sense of well-being. We hypothesize that appetite suppression and circumferential reduction through laser acupuncture can help people achieve better self-control in diet and exercise. If our hypothesis is correct, laser acupuncture may play a role in encouraging subjects to adhere to changes in behavioral lifestyle.

Previous research has suggested that gender moderates the psychological and behavioral variables on weight loss treatment [25]. However, the relevance of gender on weight loss differences with respect to laser acupuncture remains unexplored. Unlike previous studies, we will equalize the sample sizes of the two genders to help elucidate this substantial variability in outcomes. This trial seeks to provide clinical data on the effect of laser acupuncture on BMI, body fat, WHR, body contour, appetite and quality of life in the obese. Results of this trial will help clarify the value of laser acupuncture as a treatment option for individuals suffering from obesity.

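### As worded, the SF-36 schedule has no assessment at the end of period 1 or the start of period 2, so the within-person laser-versus-sham comparison is lost for this secondary outcome

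*Protocol article*

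**What the plan says.** The SF-36 is listed among the secondary outcomes in the Outcome assessment section, and its timing is given there: "Each subject will answer the SF-36 questionnaire before the trials, immediately after the trials and 2 months after the last treatment".

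The other clinical assessments follow a denser schedule. Besides the assessment before the trials, the Follow-up section has them "once every 2 weeks during the treatment, and 2 months after the last treatment", which covers both treatment periods.

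Under Study design, "the subject will be randomly assigned to 1 of 2 groups in a ratio of 1:1", and after 8 weeks plus a 2-week washout "the control group will switch to the experimental group while the experimental group will switch to the control group". Every participant therefore receives both treatments.

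The Discussion says of the washout: "We extended this washout period to 2 weeks to further reduce potential carryover effects". It also sets out what the trial is expected to deliver: "Through this study we will be able to determine whether or not laser acupuncture can alter regional adiposity, body contour and sense of well-being".

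**The concern.** A crossover earns its efficiency by comparing each participant under laser with the same participant under sham. That needs a score that belongs to each period. If the first SF-36 after baseline comes when both periods are over, no participant has a score that reflects only one treatment.

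Three things follow:

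- The paired before/after test in the Statistical analysis section would, for the SF-36, measure the joint effect of laser, sham and elapsed time.
- The only randomised comparison left is between sequences, with the precision of a parallel-group trial and no protection against carryover.
- The Discussion's expectation about well-being would rest on that weaker comparison.

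A questionnaire that was not given cannot be recovered at analysis, so the schedule has to be right during conduct.

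**Working it through.** **Inputs.** Period length 8 weeks and washout 2 weeks (Study design). Minimum total sample size 92, so n = 46 per sequence; planned 104, so 52 per sequence (Sample size). The correlation rho between a participant's SF-36 scores is not given; 0.2 to 0.7 is assumed. Standard errors are in units of the SF-36 standard deviation.

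**Step 1: timeline.** 8 + 2 + 8 = 18 weeks. Two months is about 8.7 weeks, so the last visit falls at about week 26.7.

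| Week | Laser first | Sham first | SF-36 as worded |
|---|---|---|---|
| 0 | untreated | untreated | yes |
| 8 | end of laser | end of sham | no |
| 10 | after washout | after washout | no |
| 18 | end of sham | end of laser | yes |
| 26.7 | 18.7 weeks past laser | 8.7 weeks past laser | yes |

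At the last visit one sequence is 10 + 8.7 = 18.7 weeks (about 4.3 months) past laser and the other about 2 months. Neither is a sham-only group.

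**Step 2: what can be estimated.** Let tau be the laser-minus-sham effect and lambda the carryover of first-period laser. At week 18 the sham-first sequence has expectation (mean + time effect + tau), and the laser-first sequence (mean + time effect + lambda). Their difference is tau − lambda.

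- Schedule as worded: a rank check of the design matrix shows tau estimable if lambda = 0 and not estimable once lambda is allowed.
- Scores at weeks 0, 8, 10 and 18: tau is estimable with or without a first-order carryover term, because week 8 gives a comparison that no earlier treatment can have affected.

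**Step 3: precision.**

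- Between sequences at week 18, unadjusted: SE = sqrt(2/n) = sqrt(2/46) = 0.209.
- The same, baseline-adjusted: SE = sqrt((2/n)(1 − rho²)). At rho = 0.5: sqrt(0.04348 × 0.75) = 0.181.
- Within-person crossover contrast of end-of-period scores, no carryover term: SE = sqrt((1 − rho)/n). At rho = 0.5: sqrt(0.5/46) = 0.104.

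The ratio of the adjusted to the crossover variance is 2(1 − rho²)/(1 − rho) = 2(1 + rho).

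| rho | Unadjusted SE | Adjusted SE | Crossover SE | Variance ratio, adjusted to crossover |
|---|---|---|---|---|
| 0.2 | 0.209 | 0.204 | 0.132 | 2.4 |
| 0.5 | 0.209 | 0.181 | 0.104 | 3.0 |
| 0.7 | 0.209 | 0.149 | 0.081 | 3.4 |

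**Step 4: detectable difference.** For 80% power at two-sided 5%, multiply the SE by 2.802. At week 18 this gives 0.58 SD unadjusted, or 0.57, 0.51 and 0.42 SD adjusted (rho 0.2, 0.5, 0.7). The crossover contrast gives 0.37, 0.29 and 0.23 SD. For an illustrative difference of 0.5 SD, the unadjusted week-18 comparison has 67% power with 46 per sequence and 72% with 52.

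**The case against.** **The wording may mean something else.** The Sample size section describes the trial as lasting only 8 weeks, although the two periods and washout take 18. In that usage a trial is one period, and before and after the *trials* could mean before and after each period, which is the schedule recommended here. The flowchart, which might settle this, is not available. This stands as a reason for caution, but the reading is the weaker one. Study design uses the same plural for the whole study when it names the hospital, and calls the periods phases. The third occasion, 2 months after the last treatment, cannot occur within each phase because the washout is only 2 weeks. If the per-period schedule is intended, the text still needs to say so.

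**A reader might infer that laser versus sham cannot be estimated at all for the SF-36.** That goes too far. At week 18 one randomised sequence has just finished laser and the other sham, so their comparison estimates the treatment effect if carryover is zero. A conventional crossover analysis also relies on that assumption, and the washout was lengthened to support it. The loss is the within-person contrast, precision and any check on carryover, not all information.

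**A reader might also infer that the 2-month visit is a design error for every outcome.** The article does not designate that visit as a laser-versus-sham test, and its repeated measures analysis is described over 8 biweekly points in 16 treatment weeks. A late follow-up visit in a crossover is legitimate; the caution concerns only how its results are interpreted.

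**Conclusion.** The point holds in limited form. On the natural reading, the within-person comparison is lost for one named secondary outcome, and the week-18 comparison of sequences that remains cannot be separated from carryover using SF-36 data. If a laser effect persists in the same direction, that comparison is pulled towards zero. Its variance, after baseline adjustment, is about 2.4 to 3.4 times that of the crossover contrast.

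These figures assume 46 completers per sequence, equal variances across occasions and rho between 0.2 and 0.7; the crossover standard errors also assume no carryover. The conclusion depends on reading the three occasions as spanning the whole study, which the text favours but does not settle.

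Severity is moderate. BMI, the primary outcome, and the other clinical assessments are measured every 2 weeks during treatment, so their laser-versus-sham comparison does not depend on the SF-36 schedule. Of the three aims in the quoted Discussion sentence, only well-being is affected.

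**What to change.** State that the SF-36 is given at the start and end of each 8-week period (weeks 0, 8, 10 and 18) and at 2 months after the last treatment. Analyse the period scores as a within-person crossover outcome with treatment and period effects. Report the 2-month scores, for the SF-36 and the clinical assessments, by sequence, and do not interpret them as laser versus sham. If the SF-36 is already given in each period, only the wording needs to change.

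The cost is two extra short questionnaires per participant, at times when participants already attend: the last biweekly assessment of period 1 and the first session of period 2. The Trial status section says recruitment is under way, so the change can still be made. Anyone already past week 8 or 10 would lack those scores, and the report should give their number by sequence.

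### As naturally read, the SF-36 schedule has no form at the end of period 1, so the crossover gives quality of life no within-subject laser-versus-sham contrast

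*Protocol article*

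**What the plan says.** Under Study design the trial is a two-period crossover: "This study proposes a patient-assessor-blinded, randomized, sham-controlled crossover trial with a 2-week washout period between each crossover phase". Each period lasts 8 weeks, and the arms then exchange treatments: "After 8 weeks of treatment and a 2-week washout period, the control group will switch to the experimental group".

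Under Outcome assessment the SF-36 is a named secondary outcome: "Secondary outcome measurements include waist circumference, hip circumference, WHR, body fat percentage, hunger and a Short-Form 36-item Health Survey (SF-36". The clinical assessments other than the SF-36 follow a dense schedule: "These clinical assessments will be performed before the trials, once every 2 weeks during the treatment, and 2 months after the last treatment". The next paragraph gives the SF-36 a separate and thinner one: "Each subject will answer the SF-36 questionnaire before the trials, immediately after the trials and 2 months after the last treatment". The Follow-up section repeats the biweekly schedule without mentioning the SF-36.

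Quality of life is part of the stated aim, and the Discussion makes a firm promise: "Through this study we will be able to determine whether or not laser acupuncture can alter regional adiposity, body contour and sense of well-being".

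**The concern.** A crossover gains its precision from seeing each subject under both treatments. That requires a measurement at the end of each period. For the SF-36, the schedule appears to supply one at the end of period 2 only.

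The before/after paired t-test named under Statistical analysis would then measure, in every subject, the sum of laser, sham and elapsed time. The two-month form does not help, because by then both sequences have received both treatments. The Student's t-test between groups could still compare the sequences at the end of period 2. However, the laser-first subjects would by then be 10 weeks past laser, and no period-1 SF-36 would exist as a carryover-free comparison. The Discussion itself recognises carryover as a possibility. A form that was never completed cannot be recovered by any later analysis plan.

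**Working it through.** **1. Which visits does the SF-36 sentence describe?** Count weeks from the start of treatment: period 1 is weeks 0-8, washout weeks 8-10, period 2 weeks 10-18.

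- The opening time point uses the same words as the single pre-study baseline in the clinical-assessment and Follow-up schedules.
- The closing time point, two months after treatment ends, cannot follow period 1, because period 2 starts after a 2-week washout.
- The sentence therefore most naturally describes one pass through the whole study: week 0, week 18 and two months later.

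**2. What can be estimated from those visits?** Take a model with sequence, visit, treatment (τ) and first-order carryover (λ) terms, and check the rank of its design matrix.

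| SF-36 visits | τ estimable with λ in the model | Only τ − λ estimable | τ estimable if λ = 0 |
|---|---|---|---|
| Baseline, week 18, follow-up | no | yes | yes |
| Week 8 added | yes | no | yes |

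With the visits as naturally read, the between-sequence difference at week 18 estimates treatment minus carryover, and no within-subject difference can be formed.

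**3. Inputs for the size.** The document gives no SF-36 calculation to reproduce. From Sample size I borrow 92 subjects as completers (46 per sequence), f = 0.25, which for two groups is d = 2 × 0.25 = 0.5, and correlation ρ = 0.2. These are general planning values, not SF-36 data, so ρ = 0.5 and 0.7 are shown as well. The same ρ is assumed between any two visits. SD = 1 and two-sided α = 0.05, with noncentral t on 90 df (89 for ANCOVA). Whether 92 follows from its stated inputs is a separate matter. It serves here only as a head count.

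**4. Standard errors.**

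- Week-18 t-test: √(4/92) = 0.209
- Week-18 ANCOVA on baseline: √(4(1 − ρ²)/92) = 0.204, 0.181, 0.149 at ρ = 0.2, 0.5, 0.7
- Crossover contrast: √(2(1 − ρ)/92) = 0.132, 0.104, 0.081

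The variance ratio to the crossover is 2/(1 − ρ) = 2.5, 4.0, 6.7 for the t-test, and 2(1 + ρ) = 2.4, 3.0, 3.4 for ANCOVA.

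**5. Power at d = 0.5, no carryover.**

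| ρ | Week-18 t-test | Week-18 ANCOVA | Crossover |
|---|---|---|---|
| 0.2 | 66% | 68% | 96% |
| 0.5 | 66% | 78% | >99% |
| 0.7 | 66% | 91% | >99% |

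**6. Persistence, applied to both designs.** At week 18 the laser-first group is 2 + 8 = 10 weeks past laser. Suppose a fraction c of the effect remains.

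- The expected week-18 difference is 0.5(1 − c).
- In the crossover, the laser-first sequence contributes 0.5(1 − c) and the sham-first sequence 0.5. Their average is 0.5(1 − c/2).

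At ρ = 0.2:

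| c | Week-18 difference | t-test / ANCOVA power | Crossover difference | Crossover power |
|---|---|---|---|---|
| 0 | 0.50 | 66% / 68% | 0.500 | 96% |
| 0.5 | 0.25 | 22% / 23% | 0.375 | 80% |
| 1 | 0 | 5% (α only) | 0.250 | 47% |

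The values of c are illustrative. The document gives none.

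**The case against.** **The wording is loose.** Sample size describes the trial as lasting only 8 weeks, which is one period, and elsewhere the study is usually a trial in the singular. The plural in the SF-36 sentence could therefore mean the two periods, with a form after each. The study flowchart is not available to settle it. This stands as far as it goes: a reader might infer that the SF-36 is certainly never collected at week 8, and the document does not prove that. The whole-study reading remains the more natural one for the reasons in step 1, and on either reading the visits need to be stated.

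**A randomised comparison survives.** A reader might infer that the trial has no laser-versus-sham comparison of quality of life at all. That is too strong. The sequences were randomised, and their week-18 difference is a valid treatment comparison if carryover is absent.

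**The loss can be overstated.** Baseline SF-36 is collected, so adjustment is possible although the article names only t-tests. At ρ = 0.7 it brings week-18 power to 91%. Persistence also weakens the crossover contrast, so it must be charged to both designs, as in step 6. A lasting benefit becomes indistinguishable from no benefit at week 18 only if the effect persists in full.

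**The repeated-measures ANOVA is not at issue.** One might object that it cannot be run on an outcome with three time points. However, it is planned for the clinical indices "across the 8 data collection points (treatments for 16 weeks, followed-up evaluation biweekly"), and nothing states that the SF-36 enters it.

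**Scale.** This is one secondary outcome in a self-described pilot. BMI and the outcomes measured biweekly are unaffected.

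**Conclusion.** The point holds on the natural reading of the schedule. Followed that way, the SF-36 gives no within-subject laser-versus-sham contrast, and the only treatment comparison left is between sequences in period 2, confounded with carryover.

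The cost is moderate to large, depending on the correlation and on persistence. Without carryover, power is 66% for the t-test, or 68% to 91% with baseline adjustment, against 96% or more. With half the effect persisting at ρ = 0.2, it is 22-23% against 80%. These figures rest on 92 completers, d = 0.5 and a common correlation, none of them specific to the SF-36. The loss of the within-subject contrast rests on the visit schedule alone.

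It should be acted on: quality of life is in the aim, the Discussion promises an answer on well-being, and the missing data could not be recovered later.

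**What to change.** In Outcome assessment, add the SF-36 at the last biweekly visit of period 1 (week 8) and keep the three existing forms. Compare laser with sham within subjects on the end-of-period Physical and Mental Component Summaries, with period as a factor. Report period 1 alone as the carryover-free comparison.

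If the second time point already means after each 8-week period, say so in that sentence; no new form is then needed.

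If no form is added, state in the Discussion that the SF-36 comparison is between sequences in period 2 only and is confounded with carryover. The well-being claim need not be withdrawn, but it must carry that limitation.

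The cost is one schedule line, a short amendment and a few minutes of each subject's time at a visit in the biweekly schedule. The article says the trial is still recruiting, so later subjects would benefit. Any subject already past week 8 will lack the form.
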